**CHAPTER THREE – METHODOLOGY**

**3.1 Study Site**

The study would be conducted in the Kumbungu district of the Northern region. Kumbungu means “I have killed my donkey”. The northern region was selected because, it has one of the highest prevalence of anaemia in children under five. Several activities by Non-Governmental Organizations (NGOs) at addressing the problem of anaemia have shown little improvement. The Northern region has 26 districts. The Kumbungu district has been chosen for the study because of its high prevalence of anaemia in children under five.

Kumbungu district is one of the smallest districts within the northern region with a total landmass of 1599 Square Kilometres. Kumbungu has 39,341 inhabitants within 4,133 households and a sex ratio of 100.2 males per 100 females. Children constitute 48.4% of the population. 7,101 of the population of Kumbungu are aged 0 to 4 years [70]. Average household size in Kumbungu is 9.5. The total fertility rate, crude birth rate and general fertility rate for the district are respectively 3.6, 23.4 per 1000 and 103.9 births per 1000 women aged 15 – 49. The household structure is mainly that of extended family system accounting for 71.8% of the household population while nuclear family system accounts for 14.6%. According to the recent census, only 15.2% of the population is literate in English language and 63.8% of persons aged 3 years and older in the district have never attended school. With regards to employment status, only 1.7% of the total population are employees. Majority of the working population are in farming related occupations. The district has 115 communities, most with a population below 500. Only two communities have population above 5000. With regards to housing, 79.4% of the inhabitants in the district live in thatch/palm/raffia roofed houses [70]. The district houses the only major water treatment in the northern region.

[figure not shown]

Figure 3.1: Map showing Kumbungu district

**3.2 Study design**

This study will be a community-based cluster randomized, controlled trial, with two parallel arms. Included communities shall be randomly selected. Cluster assignment is at the level of household for the locally available dietary (LAD) intervention. The study would follow the closed cohort of eligible households with children aged between 6 to 56 months at baseline for 12 weeks. All eligible children within the household would be included in the study. The interventions would be administered throughout the 12 consecutive weeks of the study. Primary outcome data would be collected at baseline (pre-intervention) and then at the end of 12 weeks (post intervention). Eligible children within the household are the unit for analysis and the clustering would be taken into account.

Cluster randomization was chosen for practical reasons and also to minimize contamination. Children of the same household eat from the same pot. Since the study assess behavioural change communication targeting intake and avoidance of enhancers and inhibitors of iron absorption, it was more appropriate to randomized at the level of the cluster, instead of individual randomization. LAD intervention would be administered at household cluster level. Households must have at least a child aged 6 – 56 months at baseline.

***3.2.1 Study Arms***

1. Iron + Folic Acid (IFA arm): Standard care arm
2. Iron + Folic Acid + Locally available dietary intervention (IFA+LAD arm): Standard Plus

**3.3 Interventions**

Intervention pertains to both cluster and individual level. At the cluster level, randomised household would each received targeted LAD intervention aimed at promoting the intake of locally available iron, folate and vitamin B12 rich foods, food rich in enhancers of iron absorption and discouraging the intake of food rich in inhibitors of iron absorption. The rest of the interventions are targeted at the individual participant level. All study participants would receive the current practiced standard treatment for anaemia; iron + folic acid.

The standard care arm would receive only the iron plus folic acid syrup. The standard plus arm (arm two) would receive iron, folic acid syrup treatment plus LAD intervention. All two arms of the study would run parallel and would be randomized in the ratio 1:1. The dosage of Iron and folic acid to be dispensed would be according to the current WHO recommended dose for age of the child [26].

Each study participant is required to take the prescribed doses daily. Monthly iron and folic acid requirement shall be dispensed to mothers/guardians. A member of the study team shall visit each household every week to monitor the administration of the iron and folic acid. Behavioural change communication administered at household level shall include a set of five points counselling guideline promoting the intake of food rich in enhancers of iron absorption and discouraging the intake of food poor in enhancers iron absorption. This guideline would be administered monthly to randomized households in a LAD arm. In all mothers/guardians of households randomized for LAD would receive three monthly BCC counselling. A monthly semi-quantitative assessment of intake of iron, folic acid and vitamin B12 intake as well as known inhibitors/enhancers of iron absorption of iron intake shall be determined at baseline (week 0), and then weeks 4, 8 and 12.

**3.4 Description of Study Population**

Study participants are children aged 6 to 56 months. Children less than six months are expected to be exclusively breastfed according prevailing guidelines. Promoting behavioural change communication that promotes intake of enhancers of iron absorption and avoiding the intake of inhibitors of iron absorption would not be appropriate in the below 6-month age group. Participants must also be less than 56 month of age at baseline because the intervention is expected to last for three months and it is expected that, participant recruited must be below five years at post intervention. Children within selected household 6 to 56 month at baseline are eligible for inclusion in the study.

Study participants above three years may be enrolled in a preschool. Enrolment in a pre-school does not affect inclusion in the study. However, data on pre-school enrolment would be collected. Most of the study participants are from poor resource setting. Both males and females have equal chance of inclusion in the study. Typically, each household consist of about 9 family members of which children below five years constitute about 2 per household.

**3.5 Inclusion and Exclusion criteria**

***3.5.1 Inclusion criteria***

***3.5.1.1 Inclusion criteria at cluster level***

At the cluster level, household inclusion to the study must satisfy the following:

1. Household within the selected community.
2. The household must have at least a child aged 6 to 56 months.

***3.5.1.2 Inclusion criteria at the participant level;***

1. All children within the eligible household aged 6 to 56 months at baseline.
2. Haemoglobin concentration measured at baseline should be less than 11.0 g/dl.
3. The child should be residing in the selected community for at least the past three month.
4. Must have a legal guardian capable of providing informed consent.

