**3.10 Randomization: sequence generation, stratification and blocking**

The data from the baseline survey would be used for sequence generation. Clusters would be stratified by mean household haemoglobin. Using the mean household haemoglobin, the clusters would be stratified into Level I; 10.0 g/dL ≥ Hb ≤ 10.9 g/dL, Level II; 7.0 g/dL ≥ Hb ≤ 9.9 g/dL, and Level III Hb < 7.0 g/dl

Households would be ordered alphabetically using household head’s surname. The ordered alphabetical name would be imported in to a statistical computer software STATA V.11 at the community health department, school of public health, University of Ghana. The program would generate a series of blocks of varying size (four, eight and twelve) for each stratum and allocate the household clusters to study arm randomly within each block [72]. Consent to randomize would be obtained at the cluster level from the household head.

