**3.11 Allocation concealment mechanism and blinding**

The treatment allocation for each household would be kept in the community health department until the study sites has completed training and are ready to implement the intervention. Clusters would be identified and recruited before randomisation. All eligible patients within the cluster would be included in the study. Allocation would be concealed from the community health nurses and family head who gave consent for household to be included in the trial. Also, allocation sequence would be concealed from researchers/clinicians enrolling and assessing participants. Sequence would be concealed in a sequentially numbered, opaque sealed and stapled envelopes. Corresponding envelopes would be opened only at the time of allocation of intervention. The intervention would be prepacked and correspond to the study arm assigned to. Independent clinicians that would assess outcome would be kept blind to intervention assignment of the household.

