***3.12.1 Primary outcome***

The primary outcome measures are mean haemoglobin levels and prevalence of anaemia in study arms. The haemoglobin level would be measured using a haematological analyser that measures the full (complete) blood count. Haemoglobin would be measured at baseline and end of intervention. Mean haemoglobin concentration (Hb g/dL) and prevalence of anaemia in children: Hb <11.0 g/dL; mild anaemia (10.0 g/dL ≥ Hb ≤ 10.9 g/dL), moderate anaemia (7.0 g/dL ≥ Hb ≤ 9.9 g/dL), and severe anaemia as Hb < 7.0 g/dl would be determined at baseline and at end of intervention.

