***3.12.2.3 Clinical assessment***

Clinical assessment would be carried out at baseline and at the end of the study. It would include a general examination; oedema, pallor, jaundice, skin colour and hair changes. Systemic examination conducting cardiovascular, respiratory and abdominal examinations would be carried out looking out for abnormalities on examination. Other specific examination for micronutrient deficiency would be carried out. For vitamin A deficiency; night blindness, Xerophthalmia, conjunctival xerosis, corneal ulceration, keratomalica. A clinical assessment checklist would be used to capture data regarding clinical assessment. A clinical diagnosis of nutritional status would be made for each study participant.

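### A child's own haemoglobin below 7.0 g/dl triggers no review or referral in the protocol text shown, although such children can be enrolled and treated with age-dosed syrup at home

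*Protocol*

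**What the plan says.** - **Entry.** Section 3.5.1.2 requires "Haemoglobin concentration measured at baseline should be less than 11.0 g/dl" and gives no lower bound. The three exclusions in 3.5.2 are febrile infective illness, diagnosed haemoglobinopathy and iron in the previous month. Section 3.11 adds: "All eligible patients within the cluster would be included in the study".
- **Severity.** Section 3.6 defines severe anaemia as Hb below 7.0 g/dl.
- **Treatment.** Both arms receive iron and folic acid. Section 3.3 states: "The dosage of Iron and folic acid to be dispensed would be according to the current WHO recommended dose for age of the child". A month's supply at a time goes to the mother or guardian, and a weekly household visit checks that it is given.
- **Use of baseline Hb.** Section 3.10 states: "The data from the baseline survey would be used for sequence generation" and "Clusters would be stratified by mean household haemoglobin". The lowest stratum is "Level III Hb < 7.0 g/dl".
- **Schedule.** Section 3.12.1 states: "Haemoglobin would be measured at baseline and end of intervention". Section 3.12.2.3 states: "Clinical assessment would be carried out at baseline and at the end of the study". Table 3.1 places both at weeks 0 and 12 only.
- **Clinical contact.** Under 3.12.2.3 and 3.13, a physician specialist examines the children. The stated products are a completed checklist and a diagnosis of nutritional status. Section 3.13 also lists adverse events, morbidity and mortality among the data to be collected.

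**The concern.** The plan expects severely anaemic children: it defines the category, gives it a randomisation stratum and reports its proportion in 3.20. The trial will therefore hold a laboratory result identifying such a child before treatment starts. Yet the entry, dosing and visit rules can all be followed to the letter while nobody is told to act on that result, and neither Hb nor a physician's examination is scheduled again until end-line.

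The protocol states the stakes itself. Section 2.2 describes severe anaemia as a leading cause of illness and death in under-fives in sub-Saharan Africa, and 2.3.1 links Hb of 5.0 g/dl or lower strongly to child mortality. The entry rule admits such a child too. Under the text shown, whether the child is referred depends on individual initiative.

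**Working it through.** Most of this check is a reading of the text. Arithmetic only illustrates its scale.

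**1. Can a child with Hb below 7.0 g/dl be enrolled?** Yes. For example, 6.5 is below 11.0 (3.5.1.2), none of the three exclusions in 3.5.2 concerns a low Hb, and 3.11 takes every eligible child in the household.

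**2. Does severity change the treatment?** No. Section 3.3 sets the dose by age.

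**3. Does the 7.0 g/dl threshold lead to any action before treatment?** Only in 3.10, and there on the household mean. Take two eligible siblings at 6.5 and 9.5 g/dl:

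(6.5 + 9.5) / 2 = 8.0 g/dl

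This falls in Level II (read as 7.0 to 9.9, as in 3.6), so the stratum does not show that one of the two is severely anaemic. Where it does reflect the child's own value, as in a household with one enrolled child, its only effect is on allocation.

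**4. Does any other text shown link a child's Hb to an action?** The sections on eligibility, intervention, randomisation, outcomes, clinical assessment, data collection, ethics, monitoring and analysis were read for a referral, rescue, withdrawal or notification rule. None was found. The nearest items are:
- the physician's examination, with no stated link to the blood count;
- the weekly visit, whose stated purpose is to monitor syrup use;
- adverse events, recorded as data with no action attached;
- a general promise in 3.17 to attend to the needs of children.

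**5. How many children might this concern?** The total of 184 is 2 × 92 from section 3.7. That figure can be approximately reproduced. For 82% versus 62%, two-sided 5% and 80% power, 78 per arm are needed. With the design effect of 1.03 and 15% added for dropout and contamination, 78 × 1.03 × 1.15 = 92.4. The figure only sets the scale here; the point does not depend on it.

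Section 2.2.1 gives 71% anaemic and 5% severe for west and central Africa in 2011. It does not make the denominator of the 5% fully clear.

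| Severe share among enrolled children | Source | Expected of 184 |
|---|---|---|
| 5% | 2.2.1, if 5% is of anaemic children | 0.05 × 184 = 9.2 |
| 5/71 = 7.04% | 2.2.1, if 5% is of all children | 0.0704 × 184 = 13.0 |
| 2% | assumption | 0.02 × 184 = 3.7 |
| 1% | assumption | 0.01 × 184 = 1.8 |

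The chance of at least one such child is 1 − (1 − p)^184, treating children as independent. It is 0.976 at 2% and 0.843 at 1%. The regional figure describes a general population. The trial excludes febrile infective illness and diagnosed haemoglobinopathy, and sections 2.2.3.2 and 2.2.3.3 name haemoglobinopathy and malaria as causes of anaemia. The enrolled share may therefore be lower.

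**The case against.** **The file is incomplete.** Consent pages were removed, the appendices shown begin at Appendix 2, and the protocol delegates detail to a data collection management plan (3.14.2), a nursing and follow-up training class (3.14.4), a clinical checklist (3.12.2.3) and a field manual (3.18). A referral step could sit in any of these. This stands: it limits the point to the text shown and lowers its weight. It does not remove the point, because what happens to a child with a severe screening result belongs with the eligibility and treatment rules.

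**There is clinical cover.** A physician looks for pallor, oedema and cardiovascular or respiratory signs, households are seen weekly, and both arms receive what 3.3 calls standard treatment. This also stands. A reader might infer that severely anaemic children go untreated, unseen or barred from outside care. The documents do not support that. What is absent is an instruction triggered by the Hb value.

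**Enrolling severe cases may be deliberate.** Sections 3.6, 3.10, 3.12.1 and 3.20 are consistent with that, and an upper-only limit contradicts nothing. A reader might infer that these children must be excluded, or that Level III is faulty because it can miss a severely anaemic child. Neither follows. Level III is an allocation stratum and was never meant to identify individuals. It matters here only because no other rule acts on the threshold before treatment.

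**Conclusion.** The point holds for the text shown. The protocol admits children with Hb below 7.0 g/dl, treats them at home on a dose set by age, schedules no Hb or physician re-check before end-line, and attaches no review or referral to the child's own result.

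The number affected is unknown. It is about 9 of 184 if the regional 5% applied directly to enrolled children, and possibly fewer after the exclusions. The 1% and 2% shares are assumptions without a source in the protocol. They show only that at least one such child is likely even at low shares.

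This is a participant-safety point that should be fixed. It is not a statistical error, and it does not touch the sample size or the validity of the comparison. A stronger grade is not warranted while the consent pages, Appendix 1 and the field manuals remain unseen.

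**What to change.** Add to section 3.13 that the physician specialist already on the team reviews each child's own Hb (not the household mean) before syrup is dispensed, and again when end-line results arrive, and refers any child below 7.0 g/dl for clinical care. The cut-off is the protocol's own. State that referred children may stay in the trial and are analysed as randomised, in line with the intention-to-treat analysis in 3.20, and that care received outside the trial is recorded. If the consent form or a manual already contains such a rule, move it into 3.13 or cite it there.

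The cost is small. The physician and the blood count already exist, and baseline Hb must be available before allocation because 3.10 stratifies on it. The first review can therefore precede allocation and leave blinding intact, and the second follows the outcome measurement. The downsides are a short delay before dispensing and some outside treatment in a few children, which could affect their end-line Hb and is the reason to record it.

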***3.5.2 Exclusion criteria***

Eligible children with any of the following would be excluded from the study:

1. Current infective illness (example; respiratory infection, diarrhoea) with fever; however, children may be rescreened again after recovery if otherwise eligible. Current infective illness would be assessed from self-reported and verification of available medical records.
2. Diagnosed case of any clinical haemoglobinopathy (eg, beta-thalassemia major, HbE-beta thalassemia, Sickle cell disease). This will be assessed based on self-report and available medical and laboratory records.
3. Received iron supplements or iron-containing MMP in the previous month.

**3.6 Definition of variables of the study**

For the purpose of this study, anaemia would be defined according to the World Health Organization’s (WHO) haemoglobin level to diagnose anaemia in children 6 to 59 months at sea level. Based on the classification; haemoglobin level less than 110 grams per litre (11 grams per decilitre) is considered as anaemia. Mild, moderate and severe anaemia are respectively defined as haemoglobin level range of 10.0 to 10.9, 7.0 to 9.9 and lover than 7.0 grams per decilitre (g/dl) [17]. A household is as defined by the Ghana statistical service; a person or a group of persons, who live together in the same house or compound and share the same housekeeping arrangements.

**3.7 Sample size calculation**

The sample size was calculated to determine the minimum difference in prevalence of anaemia between arms of the study. The following information was used:

1. Estimated prevalence of anaemia at baseline is 82%, and an estimated 20% reduction after 12 weeks.
2. Estimated average cluster size; which is the average number of children per household is 1.7 (≈2) obtained by the ratio of number of children aged less than five years (7,101) to the number of households in the district (4,133).
3. An estimated intra-cluster correlation (ICC) of 0.010
4. Estimate of coefficient of variation of cluster sizes of 0.90
5. Power of at least 80% (0.80)
6. Significance level of 5% (0.05)
7. Allowing for a cluster randomization design effect of 1.03 and
8. A dropout rate of about 5% for the 12 weeks period,
9. A contamination effect of 10%

With the above considerations, and using a menu driven facility for sample size calculation in cluster randomized controlled trial [71] available as add-on in STATA (version 11.1, StataCorp, Special Edition, College Station, Texas 77845 USA), the minimum sample size and number of cluster per arm was calculated. The computation made use of the following formula for calculating the number of clusters (households) [71]:

$$k=1+\frac{n_{i}}{m}+\mathrm{CVIF}$$

Where

$$\mathrm{CVIF}=\frac{{cv}_{clusters}^{2}\left( \mu_{1}^{2}+ \mu_{2}^{2} \right)\left( z_{\alpha/2}+z_{\beta} \right)^{2}}{d^{2}}$$

And

k = number of clusters required per study arm

$n_{i}$= number of sample size required under individual randomization

*m* = number of clusters required per arm

*d* = pre-specified difference

${cv}_{clusters}$= intra-cluster correlation (ICC) coefficient

$z_{\beta}$ =Maximum available power

$z_{\alpha/2}=$Denotes the upper ${100}_{\alpha/2}$ standard normal centile

$\mu_{1} and \mu_{2}$ = mean/proportion per study arm

The minimum sample size per arm is 92 and the number of clusters per study arm is 54 households (minimum sample size/ average cluster size= 92/1.7). Considering this study proposes two parallel arms, the total minimum study sample size is 184 and the minimum number of households is 108 households.

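### If 10% contamination dilutes the effect, 92 children per arm give about 74–77% power on the plan's other inputs, not at least 80%

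*Protocol*

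**What the plan says.** Section 3.7 (Sample size calculation) sizes the trial on anaemia prevalence: "Estimated prevalence of anaemia at baseline is 82%, and an estimated 20% reduction after 12 weeks". It lists an average of 1.7 eligible children per household, "An estimated intra-cluster correlation (ICC) of 0.010", "Estimate of coefficient of variation of cluster sizes of 0.90", 5% significance, power of at least 80%, a design effect of 1.03, dropout of about 5% over 12 weeks, and "A contamination effect of 10"%.

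The result is: "The minimum sample size per arm is 92 and the number of clusters per study arm is 54 households", or 184 children and 108 households in total.

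Contamination is not defined. Neither the printed formula nor the stated effect contains a dilution term, and no intermediate step is shown. Section 3.20 (Data Analysis) plans intention-to-treat and per-protocol analyses. Section 3.2 (Study design) gives limiting contamination as one reason for randomising households, adding: "Children of the same household eat from the same pot".

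**The concern.** Dropout and contamination act differently. A child who drops out supplies no endpoint, and enrolling more children compensates. A control child whose household picks up the dietary advice is still measured and still counted as a control under intention to treat. The arms move closer together, and required sample size rises with the inverse square of the difference: a difference cut to 0.9 of its size needs about 1/0.81 = 1.23 times as many children, not 1.10 times.

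Contamination is a realistic risk here. Households of both arms lie in the same few communities (3.8.1, 3.10), the intervention is dietary advice, and one community health nurse is responsible for each community (3.13). If 92 allows for contamination only as headcount, the power promised for a primary outcome is not delivered by the assumptions listed beside it.

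**Working it through.** **Inputs (all section 3.7).** 82% and a 20% reduction, read as 20 percentage points (0.82 v 0.62); two-sided 5%, because the formula uses z at α/2 (1.960); power 80% (0.8416); design effect 1.03; dropout 5%; contamination 10%.

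**1. Reproducing 92.** Pooled two-proportion formula:

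n = [1.960·√(2p̄q̄) + 0.8416·√(p₁q₁ + p₂q₂)]² / d²

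For 0.82 v 0.62, p̄ = 0.72 and n = (1.960×0.6350 + 0.8416×0.6190)² / 0.04 = 77.9, so 78. Then:

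- design effect: 77.9 × 1.03 = 80.3
- dropout as well: 80.3 / 0.95 = 84.5
- dropout and contamination added as headcount: 80.3 × 1.15 = 92.3, or 80.3 × 1.05 × 1.10 = 92.7

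The last line uses every listed input and lands on the stated figure.

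**2. The reconstruction is not unique.** The unpooled formula with a diluted difference, 0.82 v 0.64, gives (1.960 + 0.8416)² × 0.378 / 0.18² = 91.6, also 92, but leaves out the design effect and dropout. A continuity-corrected 88 × 1.05 = 92.4 uses dropout alone. With the design effect, dropout and an 18-point difference all included, the requirement is 102.2–106.9 per arm pooled, and at least 99 unpooled. Neither is 92.

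**3. Dilution.** If 10% of controls obtain the full benefit, the control rate is 0.82 − 0.10×0.20 = 0.80 and the comparison is 0.80 v 0.62. If the difference shrinks from the other side, it is 0.82 v 0.64. Either way d = 0.18.

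**4. Power at 92 per arm.** Effective n = 92 × 0.95 / 1.03 = 84.9 per arm.

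Pooled power = Φ{[d√n − 1.960·√(2p̄q̄)] / √(p₁q₁ + p₂q₂)}; for 0.80 v 0.62 this is Φ{(0.18×9.212 − 1.960×0.6417)/0.6290} = Φ(0.637) = 73.8%. Unpooled power = Φ{d/√[(p₁q₁ + p₂q₂)/n] − 1.960}.

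| Scenario | Rates | Pooled | Unpooled |
|---|---|---|---|
| No contamination | 0.82 v 0.62 | 83.3% | 84.5% |
| 10% dilution, controls shift | 0.80 v 0.62 | 73.8% | 75.1% |
| 10% dilution, LAD arm shifts | 0.82 v 0.64 | 75.7% | 76.9% |
| Half of that, controls shift | 0.81 v 0.62 | 78.8% | 80.1% |
| Half of that, LAD arm shifts | 0.82 v 0.63 | 79.7% | 81.0% |

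**5. Detectable difference.** Solving the pooled power formula for 80% at 84.9 effective per arm, with 82% in controls, gives a difference of about 19.1 points as observed after contamination. With 10% dilution, the undiluted effect would have to be about 19.1/0.9 = 21.2 points.

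**6. ICC sensitivity (values above 0.010 are assumptions).** Design effect = 1 + [(0.90² + 1)×1.7 − 1]×ICC, with 87.4 children retained per arm, pooled:

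| ICC | Design effect | No contamination | 0.80 v 0.62 |
|---|---|---|---|
| 0.1 | 1.21 | 77% | 67% |
| 0.2 | 1.42 | 70% | 60% |
| 0.3 | 1.62 | 64% | 54% |

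The table leans on the coefficient of variation of 0.90: with equal clusters of 1.7 and no contamination, ICC 0.1 gives 81.8%.

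**The case against.** **The mechanism is not documented.** A reader might infer that the plan demonstrably added contamination to the headcount. The protocol does not show this, and step 2 gives a route to 92 in which contamination was applied to the effect. This stands, and the headcount explanation is only the best fit. It does not rescue the power: the alternative route omits the design effect and dropout, and once they are restored power is about 77%.

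**Contamination may be partial.** The intervention is three monthly counselling sessions, and a control household may absorb only part of the advice. With half the effect, power is about 79–81% and the shortfall all but disappears. This also stands, and it is why the 10% needs a definition.

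**The ICC.** A reader might take the shared pot as contradicting an ICC of 0.010 and conclude that true power is between 54% and 67%. The documents do not support that. The sentence justifies randomising by household and says nothing about residual correlation in anaemia status; the higher ICCs come from no source in the protocol.

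**The base rates are themselves doubtful.** Section 3.5.1.2 admits only children with haemoglobin below 11.0 g/dl, so 82% is not the baseline prevalence among those enrolled. Section 3.20 separately claims 90% power for other outcomes. Both are separate matters. They mean that any restated power is conditional on the rates in section 3.7.

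**Conclusion.** The point holds in a conditional form. Taking the listed inputs at face value and reading 10% contamination as a 10% shrinkage of the difference, 92 per arm gives about 74–77% power, roughly 3 to 6 points below the stated minimum. Reaching 80% would take about 102–107 per arm by the pooled formula, some 10 to 15 more than planned.

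This rests on a 20-point absolute reduction, a two-sided 5% test, 5% dropout, a design effect of 1.03, and contaminated children obtaining the full effect of the other arm. Worse figures can be produced: about 64% if 10% cross over in both directions (0.80 v 0.64), and 58–60% if the 20% reduction is relative and diluted. The documents support neither. Two-way crossover is nowhere mentioned, and the relative reading does not reproduce 92, since it needs about 132–135 with the same headcount inflation.

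The shortfall is moderate. It calls for a corrected power statement and does not show that the trial cannot proceed at its planned size.

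**What to change.** In section 3.7:

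1. Define the 10%: what share of which arm is affected, and how much of the effect those children are assumed to gain.
2. State that contamination is applied to the effect and not to the headcount, for example by sizing on 80% v 62%, and show the steps from the unadjusted sample size through design effect and dropout.
3. Restate the power for 92 per arm as about 74–77% under full dilution, or give the difference detectable at 80% (about 19 points after contamination, about 21 before). If partial contamination is assumed, say so and report the corresponding 79–81%.
4. Optionally, show power over a range of ICC values, with everything above 0.010 labelled as an assumption.

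The cost is wording and perhaps one small table. The power statement becomes less favourable. No extra enrolment is required, although 184 is already described as a minimum, so the sponsor may choose to recruit more.
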